#### **Completer Cohort:**

The Completer cohort includes all patients in the ITT cohort who complete the study.

#### **Per Protocol Cohort:**

The Per-Protocol cohort includes all patients in the ITT cohort who complete the study (completed study treatment) in compliance with the protocol and have no major protocol violations.

For the ITT cohort, the Last Observation Carried Forward (LOCF) approach will be applied, when deemed appropriate, to account for missing data at or prior to study termination.

### 13.4 Comparability of Treatment Groups at Baseline

**Primary End Points** - as in section 5.1

**Observational End Points** - as in section 5.2

#### **Safety and Tolerability Assessments**

**Adverse Events:** The incidence and frequency of AEs will be presented by SOC and preferred terminology according to MedDRA dictionary. AEs will also be presented by SOC, High Level Term and preferred terminology.

Data will be tabulated by treatment group, age, maximal severity, maximal outcome, maximal action taken, and maximal relationship to the tested catheters.

SAEs and seriousness criteria will be listed and discussed on a case by case basis.

**Laboratory Tests:** The incidence of laboratory tests outside the normal range and the incidence of measurements of potential clinical significance will be presented by treatment group. Shift analysis of these counts from baseline will also be provided. Descriptive statistics as well as their changes from baseline will also be presented by study group.

**Vital Signs:** Incidence of measurements of potential clinical significance will be presented by study group. Shift analysis from baseline will be provided as well. Descriptive statistics of vital signs, as well as, their changes from baseline, will be presented by study group.

#### **Tolerability Assessments**

Tolerability analysis will be based on the number (%) of patients who failed to complete the study, the number (%) of patients who failed to complete the study due to AEs. Time to withdrawal will be presented by Kaplan-Meier curves. Significance testing of time to withdrawal will be done using Cox's proportional hazards model.

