| 
Statistical Considerations:
 | 
All measured variables and derived parameters will be listed individually and, if appropriate, tabulated by descriptive statistics. For categorical variables summary tables will be provided giving sample size, absolute and relative frequency and 95% Confidence Interval (CI) for proportions by study group.
 
For continuous variables summary tables will be provided giving sample size, arithmetic mean, standard deviation, coefficient of variation (if appropriate), median, minimum and maximum, percentiles and 95% CI for means of variables by study group.
 
Statistical Methods:
 
The study objective is to demonstrate a safety profile and tolerability. All adverse events will be coded according to coding dictionaries (MedDRA version 16.1 or higher) and presented in tables by System Organ Class (SOC) and Preferred Term (PT). Drug-related adverse events will be presented as well.
 
95% CI will be calculated for the proportion of patients who prematurely discontinued the study for any reason and due to any AE or SAE.
 
Chi-square test or Fisher's Exact test (as is appropriate) will be used for analyzing the difference in proportions between the study groups. The Paired T-test or Signed rank test for two means (as is appropriate) will be applied for analyzing changes in continuous parameters within study group.
 
The two-sample T-test or Non-parametric Wilcoxon-Mann-Whitney Rank sum test for independent samples (as is appropriate) will be applied for analyzing differences in continuous parameters between the study groups.
 
All tests will be two-tailed, and a p-value of 5% or less will be considered statistically significant.
 
The data will be analyzed using the SAS ® version 9.1 (SAS Institute, Cary North Carolina).
 |

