## 6. STUDY DESIGN

### 6.1 Overview and Plan

This is a Prospective, Phase I, Open-label Case Series, Single-Center study.

A total of 12 patients, over the age of 18, undergoing radical prostatectomy will be enrolled. Screening data will be reviewed to determine patients' eligibility and informed consents will be obtained.

Patients who meet all inclusion criteria and none of the exclusion criteria will be enrolled.

6 patients will be allocated to receive NO-impregnated Foley catheters (treatment) followed by 6 patients allocated to receive non-NO-impregnated Foley catheters (control).

A patient will receive catheter up to  $21 \pm 7$  days of study treatment. A patient is considered as completed the study "per protocol", once study treatment was completed: 30-45 days after catheterization.

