### **7.5.4 Replacement of Withdrawn Patients**

Up to 12 patients will be recruited, in order to have a sample size of at least 6 patients catheterized with NO-impregnated catheters and 6 patients catheterized with non-NO-impregnated catheters, who completed the study (see protocol).

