#### **Safety and Tolerability:**

The study objective is to demonstrate a safety and tolerability profile.

Adverse events will be coded according to coding dictionaries (MedDRA version 16.1 or higher) and presented in tables by System Organ Class (SOC) and Preferred Term (PT). Additional tables will be generated for adverse events associated with NO-impregnated catheters.

95% CI will be calculated for the proportion of patients who prematurely discontinued the study for any reason and due to any AE or SAE.

Chi-square test or Fisher's Exact test (as is appropriate) will be used for analyzing the difference in proportions between the study groups. Laboratory results will be summarized in appropriate tables by time. Changes from baseline will be calculated and presented as well.

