#### **Observational Assessment**

95% CI will be calculated for the proportion of patients with catheter-related urinary tract infections at any time point.

Chi-square test or Fisher's Exact test (as appropriate) will be used for analyzing the difference in the above proportions between the study groups.

The Paired T-test or Signed Rank test for two means (paired observations; as is appropriate) will be applied for testing the statistical significance of the changes from baseline to any post-baseline measurement in biofilm formation on the surface and bacteriuria within study group.

The two-sample T-test or Non-parametric Wilcoxon-Mann-Whitney Rank sum test for independent samples (as appropriate) will be applied for testing the statistical significance of the differences in the above parameters between the study groups.

All tests will be two-tailed, and a *p-value* of 5% or less will be considered statistically significant.

The data will be analyzed using the SAS ® version 9.1 (SAS Institute, Cary North Carolina).

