### 13.1 Sample Size Rationale

Total of 12 patients.

The planned sample size of 12 patients for the Phase I trial took under consideration the possibility of a 10% drop, as detailed in section 7.5. The planned sample size considered adequate by the sponsor and investigators for this study. The study is not expected to show statistical significance or statistical power, only demonstrate a safety profile.

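### The unconditional Cox significance test of time to withdrawal does not suit 6 patients per arm with about one expected withdrawal

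*Protocol*

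**What the plan says.** Section 13.4, Tolerability Assessments, bases tolerability on the number and percentage of patients who do not complete the study, overall and because of AEs. It adds Kaplan-Meier curves of time to withdrawal and then: "Significance testing of time to withdrawal will be done using Cox's proportional hazards model". It does not say which Cox test is meant (Wald, score or likelihood ratio), or what happens if few or no patients withdraw.

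Section 6.1 puts 6 patients on the impregnated catheter, followed by 6 on the control catheter. Sections 8.2 and 13.2 mark randomization as not applicable. The only drop-out figure is in section 13.1: "The planned sample size of 12 patients for the Phase I trial took under consideration the possibility of a 10% drop".

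For proportions, section 13 (Safety and Tolerability) says: "Chi-square test or Fisher's Exact test (as is appropriate) will be used for analyzing the difference in proportions between the study groups". The Synopsis and the Observational Assessment part of section 13 give the same pair of tests. The Synopsis also sets a general rule: "All tests will be two-tailed, and a p-value of 5% or less will be considered statistically significant". Section 13.1 states: "The study is not expected to show statistical significance or statistical power, only demonstrate a safety profile". The Synopsis (Number of Patients) and section 7.1 say much the same.

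**The concern.** A two-group Cox model has a finite hazard ratio only if withdrawals occur in both arms. With none at all there is nothing to fit. With withdrawals in one arm only, the estimate runs to zero or infinity and its standard error loses meaning. With 12 patients and few expected withdrawals, these are the likely outcomes.

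The analysis bears on tolerability, which is part of the primary objective. Section 20.2 assigns the data-management group the statistical analysis as the protocol defines it. If the sentence is followed as written, the report could carry a Wald p-value that means nothing. The analyst might otherwise choose among Cox tests after seeing the data, and those tests can fall on opposite sides of 5%.

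**Working it through.** **Inputs.** 6 patients per arm (section 6.1); a 10% drop (section 13.1); a two-sided 5% level (Synopsis and section 13). The protocol gives no formula, effect size or event target, so there is no planned event count or power figure to reproduce.

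**Assumption.** The 10% is read as a withdrawal probability d that is the same for every patient and independent between patients. The protocol does not say this.

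**How often the hazard ratio is not finite.** Let q = (1 − d)^6 be the chance that an arm has no withdrawal.

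- Expected withdrawals: 12 × 0.10 = 1.2
- q = 0.9^6 = 0.531
- No withdrawal at all: q² = 0.9^12 = 0.282
- Withdrawals in one arm only: 2q(1 − q) = 2 × 0.531 × 0.469 = 0.498
- No finite hazard ratio: 1 − (1 − q)² = 0.780

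A simulation of 40,000 two-group Cox fits (exponential withdrawal times, censoring at 45 days) gave 0.280 + 0.498 = 0.778.

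| Withdrawal rate d | No withdrawals | One arm only | No finite hazard ratio |
|---|---|---|---|
| 5% | 54% | 39% | 93% |
| 10% | 28% | 50% | 78% |
| 15% | 14% | 47% | 61% |
| 20% | 7% | 39% | 46% |
| 30% | 1% | 21% | 22% |

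Conditional on the count, one withdrawal gives no finite hazard ratio with certainty. Two withdrawals do so in 2 × C(6,2)/C(12,2) = 30/66 = 45% of cases.

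**What the Cox tests give when withdrawals fall in one arm only.** Take 3 v 0, with distinct times and no earlier censoring. The risk sets (affected arm, other arm) are (6,6), (5,6) and (4,6).

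- Wald: no usable value, because the estimate is infinite.
- Score: U = 3 − (6/12 + 5/11 + 4/10) = 1.645; V = 0.250 + 0.248 + 0.240 = 0.738; U²/V = 3.67; p = 0.055.
- Likelihood ratio: 2 × [ln(12/6) + ln(11/5) + ln(10/4)] = 4.80; p = 0.029.
- Exact permutation log-rank: 2 × C(6,3)/C(12,3) = 40/220; p = 0.18, equal to Fisher.

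The two computable Cox tests fall on opposite sides of 5%, and both are far from the exact value. At 4 v 0 the score test gives 0.018 against an exact 0.061. At 5 v 0 it gives 0.004 against an exact 0.015.

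**Rejection rates in the simulation.** With 10% in both arms: Wald below 0.01%, score 0.1%, likelihood ratio 1.6%. With 30% v 10%: Wald 0.2%, score 4.4%, likelihood ratio 14%. The fault is therefore not a high overall false-positive rate at 10%. The p-value depends heavily on which Cox test is taken, and it is poorly calibrated in the patterns where it matters.

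**Chi-square or Fisher.** With r events in total, the smallest expected count at 6 v 6 is min(r, 12 − r)/2, which never exceeds 3. The usual minimum of 5 cannot be met. The uncorrected chi-square p-value and Fisher's differ in verdict at 3/6 v 0/6 (0.046 v 0.18) and at 4/6 v 0/6 (0.014 v 0.061).

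**The case against.** **The test does not usually fail to compute.** A reader might infer from 78% that it does. The sentence asks for significance testing, not for a hazard ratio, and does not name the Wald statistic. The score and likelihood-ratio tests exist when withdrawals fall in one arm only. At a 10% rate, only the 28% of trials with no withdrawal leave nothing to test, and there no test is needed. This stands. The 78% describes the estimate and the Wald test, and the remaining tests are computable but unreliable.

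**The 10% is a soft input.** Section 13.1 speaks of a possibility, and the withdrawal grounds in section 7.5.2 are broad (insertion difficulty, catheter replacement, an SAE), so the true rate may be higher. This also stands, and is why the table gives a range. Even at 30%, about one trial in five has no finite hazard ratio.

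**Cox is supplementary.** The tolerability endpoint in section 5.1 is a proportion, and Kaplan-Meier curves are already planned. Losing the Cox sentence leaves the main analysis intact. That limits the importance of the point and makes the repair easy.

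**Chi-square is only an option.** Any ordinary reading of the appropriateness clause leads to Fisher at this size, so this part is a wording note.

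**Two further inferences are not supported.** A reader might expect non-significant results to be presented as evidence of safety. The protocol nowhere says so, and it disclaims significance and power in three places. A reader might also object to Wald confidence intervals for proportions, but the protocol asks for 95% intervals without naming a method.

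**Conclusion.** The point holds in a limited form. An unconditional Cox test is badly chosen for 6 v 6 patients. At an assumed equal, independent 10% withdrawal rate, about 78% of such trials have no finite hazard ratio, with a range of 93% to 22% for rates from 5% to 30%. In the 50% with withdrawals in one arm only, the Wald p-value is meaningless and the score and likelihood-ratio p-values are poor approximations. The general 5% rule also sits awkwardly beside the statement that significance is not expected, but this is untidiness, not a flat contradiction. The point does not undermine the descriptive safety analysis. It should be corrected because it concerns tolerability and the correction is cheap.

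**What to change.** 1. In section 13.4, Tolerability Assessments, delete the Cox sentence and keep the Kaplan-Meier curves.
2. If a p-value is wanted, specify an exact (permutation) log-rank test whenever at least one withdrawal occurs. It must not be restricted to withdrawals in both arms: that would suppress it when all withdrawals are on the impregnated catheter, where it is well defined (5 v 0 gives p = 0.015).
3. In the Synopsis and in section 13 (Safety and Tolerability; Observational Assessment), name Fisher's exact test and drop the chi-square option.
4. Replace the 5% rule with a statement that p-values are descriptive, in line with the Synopsis (Number of Patients) and sections 7.1 and 13.1. Allocation is sequential, so a permutation p-value rests on exchangeability of the two groups and not on randomization, which is a further reason for the label.

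The cost is wording in the Synopsis and section 13. No patient, visit or assessment changes.

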## **14. REGULATORY AND ETHICAL ISSUES**

### **14.1 Compliance with Regulations Applicable to Clinical Trials**

The study will be conducted according to the laws, regulations and administrative provisions relating to the implementation of good clinical practice in the conduct of clinical trials on medicinal products for human use, as applicable by national legislation (according to the Israeli Ministry of Health regulations) and EU Directives and US 21 CFR Part 11, 50, 54, 56, 312.

### **14.2 Informed Consent**

The principles of Informed Consent, according to the Declaration of Helsinki 1964 and its updates up to 1996, ICH guidelines on GCP, 21 CFR part 50 of the FDA Regulations and/or EU Directives, will be followed. The Israeli Ministry of Health template of informed consent form will be used. A patient should not enter a clinical study until he have been properly informed, have been given time to contemplate participation, and have freely given consent by signing and dating the Institutional Review Board (IRB) approved informed consent form. This must be done prior to performing any study related procedures.

The proposed consent form and any other documents relevant to the consent process must be submitted to the IRB, together with the protocol, and must be approved prior to study start.

A copy of the fully signed and dated informed consent form and any other documents relevant to the consent process will be given to the patient and the original will be maintained at the site.

The informed consent process should include an explanation in the language the patient knows fluently. The consent form should be in a language the patient can read and understand. The process should be documented in the patient's file.

Any deviation from the consent process should be approved by the IRB as well as documented.

### **14.3 Institutional Review Board (IRB)**

The study must have unconditional approval in writing, by an appropriate Review board (IRB). A copy of the letter of approval from the IRB, which contains specific identification of the documents approved, must be received by ENOX prior to site initiation.

Any amendments to the protocol or subsequent changes to the informed consent form as a result of changes to the protocol and/or investigator brochure that is approved by ENOX , must also be approved by the IRB and documentation of

this approval provided to ENOX. Records of the IRB review and approval of all documents pertaining to this study must be kept on file by the Investigator and are patient to the sponsor's audit and/or regulatory authority inspection, during or after completion of the study.

SAEs will be reported to the IRB by the investigator according to Israeli MOH regulations and the IRB requirements

Periodic status reports must be submitted to the IRB as required, as well as notification of completion of the study and a final report where applicable. A copy of all reports submitted to the IRB must be sent to the sponsor.

#### **14.4 Protocol Amendments**

Protocol amendments issued by the sponsor must be approved by the IRB and the Israeli Ministry of Health prior to implementation.

#### **14.5 Declaration of the End of the Clinical Trial**

A declaration of the end of the clinical trial will be made according to Israeli Ministry of Health regulations.

Patient Confidentiality: prior to publication, patient data listings will be removed to ensure that patient confidentiality is maintained.

In alignment with the EU Directive 95/46/EC and Israeli MOH Regulations on data protection, the patient's name will not be identifiable from the subject study code. The investigator should keep the code given in the "Patient Identification Log" (see Section 16.4.5).

After obtaining patient's consent, the investigator will permit the study monitor, independent auditor, or regulatory agency personnel to review the portion of the patient's medical record that is directly related to the study. This shall include all study relevant documentation including patient medical history to verify eligibility, laboratory tests results, admission/discharge summaries for hospital admissions occurring while the patient is enrolled in the study, and autopsy reports for deaths occurring during the study (if applicable).

#### **14.6 Liability And Insurance**

A certificate of clinical trials insurance will be provided according to the Israeli Ministry of Health regulations to the study center by ENOX.

## **15. DOCUMENTATION**

### **15.1 Study File and Site Documents**

Prior to the initiation of the study, the following items must be received by the sponsor from the site:

- 1) Confidential disclosure agreement.
- 2) Signed protocol, amendment(s) and notification(s) page(s).
- 3) The principal investigator's curriculum vitae.
- 4) Completed and signed required regulatory form (a complete submission package).
- 5) Signed clinical study agreement.
- 6) IRB-written approval for the protocol, amendment(s), informed consent form, patient Information Sheet.
- 7) EC/IRB Membership list or an official statement from the EC/IRB stating the EC/IRB is in compliance with ICH- GCP guidelines.
- 8) Financial disclosure information for all persons listed in study delegation form.
- 9) Bacteriologies laboratory quality documentation.
- 10) Relevant normal ranges of all laboratory tests done to study participants.

### **15.2 Study Documents Supplied by the Sponsor**

The sponsor will supply the investigator with the following items:

- Current version of the Investigator's Brochure
- Printed CRF and the electronic CRF in PDF format (Master CRF)
- Informed consent form – using the Israeli Ministry of Health template
- Insurance certificate
- Operations manual - for all study specific equipment

### **15.3 Maintenance and Retention of Records**

It is the responsibility of the Investigator to maintain a comprehensive and centralized filing system of all relevant documentation.

- Investigators will be instructed to retain all study records required by the sponsor and regulatory authorities in a secure and safe facility with limited access for one of the following time periods based on notification from the Sponsor
- A period of at least two years from last marketing authorization and notification from the sponsor
- Or a period of at least 15 years after discontinuation of clinical development of the investigational product as confirmed by the Sponsor
- Or longer if required by local regulations

The investigator will be instructed to consult with the sponsor before disposal of any study records and to provide written notification to the sponsor of any change in the location, disposition, or custody of the study files.

## **16. DATA HANDLING**

### **16.1 Data Collection via Paper CRF**

CRFs for individual patients will be provided by the sponsor. The CRFs are supplied on NCR paper; one copy will be kept by the investigator and the original and second copy will be retrieved by the ENOX study monitor.

CRFs are used to record study data and are an integral part of the study and subsequent reports. The data requested on the CRF must be recorded in black/blue ink (hard point pen) as the study is in progress. Additional information may be included as warranted. Any correction or deletion should be made by drawing a single line through the entry so that the original entry is still legible; this change must be initialed and dated by study staff personnel. Changes regarding AEs and clinical judgments must be initialed and dated by the investigator.

CRFs will be considered complete when all missing and/or incorrect data have been accounted for. Copies of the study records must be retained in the files of the investigator in accordance local regulations.

Completed CRFs must be signed by the investigator for each patient enrolled, including those prematurely terminated from the study for any reason. The reason for premature termination must be recorded by the investigator for each patient, on the termination visit CRF page.

CRFs must be kept current to reflect the patient's status at each phase during the course of the study. Patients should not be identified by name; appropriately coded identification and patient's non-identifiable initials must be used. The Investigator must keep a separate log of the patients' names, used initials and addresses and it must be maintained confidential.

CRFs must be completed and available for on-site review at each monitoring visit and within 14 working days of a patient's termination from the study.

All source documents, such as clinic charts, must be available to allow source data verification.

CRFs will be sent to the DMC (Data Management Center- Medistat) promptly after the visit has been monitored.

